#### 3.2 Requirements at the Trial Sites Regarding Personnel and Equipment

The study management is experienced and trained in clinical trials. Similar studies (such as the IFB STEN or GluMBSE study) are currently ongoing with overlapping personnel.

All examinations (taking of blood samples, BIA measurement, MRI, indirect calorimetry, ultrasound etc.) will be performed by trained (and experienced) personnel following a detailed working instruction. All planned examinations were performed frequently in the past and are part of the daily routine. None of the above examinations is new or has to be established.

The equipment needed for the clinical trial part is available in the clinic (such as MRI, BIA equipment, indirect calorimetry etc.).

The study invasive procedure (RYGB) is well established and part of the clinical practice at our hospital.

For the scientific part, the fully equipped laboratory capacity of the Departments of Medicine, Bariatric Surgery and Laboratory Medicine will be used.

#### 3.3 Trial Sites and Number of Trial Subjects

The study is a single centre trial.

|                                        |          |
|----------------------------------------|----------|
| To be assessed for eligibility: | n = 1500 |
| To be allocated to trial:       | n = 160  |
| To be analysed:                 | n = 140  |

### 3.4 Expected Duration of Trial

#### Individual trial duration:

Duration of intervention per patient: 1 year

#### Complete trial duration:

Duration of the entire trial (months): 86

Recruitment period (months): 74

Data analysis and publication: 6 months after the last visit of the last patient

### 3.5 Premature Termination of the Trial

The trial can be terminated prematurely by the coordinating investigator in the event of

- serious adverse events
- changes in the risk-benefit considerations, e.g. as a result of unexpected adverse events
- new insights from other trials
- an insufficient recruitment rate

The final decision regarding the premature termination of the trial will be made by the coordinating investigator.

## 4 TRIAL SUBJECTS

### 4.1 Inclusion Criteria

- BMI  $\geq 27$  to  $\leq 60$  kg/m^2
- T2DM
  - for patients BMI  $\geq 35$  kg/m^2: any T2DM
  - for patients BMI  $< 35$  kg/m^2:
    - unsatisfactory medical non-insulin treatment (multiple medications, HbA1c  $> 6.5\%$ , hypo- or hyperglycaemias) or
    - planned insulin treatment or ongoing insulin treatment
- males and females, age  $\geq 18$  years
- written informed consent

### 4.2 Exclusion Criteria

- any chronic inflammatory or malignant disease
- type 1 diabetes (C-Peptide  $< 0,5$  µg/l, GAD-Ab or ICA-Ab positive)
- peptic ulcer
- contraindication for general anaesthesia
- drug or alcohol abuse
- untreated thyroid dysfunction
- pregnancy or breast feeding woman
- fertile women (within two years of their last menstruation) without appropriate contraceptive measures (implanon, injections, oral contraceptives, intrauterine devices, partner with vasectomy) while participating in the investigation
- expected non-compliance
- participation in other interventional trial

## 5 TRIAL INTERVENTION

### 5.1 Standard RYGB (stRYGB) group and Changed limb length RYGB (cllRYGB) group

Prior to surgery all candidates will be put on a low calorie (protein rich) diet for 14 days.

Roux-en-Y gastric bypass (stRYGB and cllRYGB) reduces the size of stomach to a small pouch – about the size of a walnut (pouch volume 10-20 cm^3), by stapling off a section of it. The surgeon then attaches this pouch directly to the small intestine, bypassing most of the stomach and the upper part of the small intestine.

All patients in the stRYGB group will undergo surgery with pouch size: 10 to 20 cm^3 and limb length:

- BMI  $\geq$  50 kg/m^2: alimentary limb: 170 cm, biliopancreatic limb: 80 cm).
- BMI  $\leq$  50 kg/m^2: alimentary limb: 150 cm, biliopancreatic limb: 50 cm).

All patients in the cllRYGB group will undergo bypass surgery with pouch size: 10 to 20 cm^3 and limb length:

- BMI  $\geq$  50 kg/m^2: alimentary limb: 80 cm, biliopancreatic limb: 170 cm).
- BMI  $\leq$  50 kg/m^2: alimentary limb: 50 cm, biliopancreatic limb: 150 cm).

RYGB (stRYGB and cllRYGB) will be done as a laparoscopic surgery. Laparoscopic surgery is performed using several small incisions, or *ports*: one to insert a surgical telescope connected to a video camera, and others to permit access of specialized operating instruments. The surgeon views his operation on a video screen.

[figure not shown]

Grafic 1: Standard RYGB (stRYGB)

Due to the reduced size of the newly created stomach pouch and reduced food intake, adequate nutrition demands that the patient follow the surgeon's instructions for food consumption, including the number of meals to be taken daily, adequate protein intake, and the use of vitamin and mineral supplements. Calcium supplements, iron supplements, protein supplements, multi-vitamins (sometimes pre-natal vitamins are best), and vitamin B12 (cyanocobalamin) supplements are all very important to the post-operative bypass patient.

## 5.2 Observational Control (Medical treatment group)

Patients in this group will undergo standard medical treatment for T2DM, RYGB is possible for the patient after completing the trial at 12 months.

Irrespective of the study group, all patients will be treated with antidiabetic agents as recommended by current guidelines [8], in addition to recommendations for a suitable diet and exercise. The therapies will be prescribed by an endocrinologist specialized in diabetes treatment.

In addition to patients, willing to take part in the study, patients (only year 2016) out of the

loss program within an program exclusively financed with the [REDACTED] registered by ethical vote [REDACTED] For these patients the duration of Visit 5 is 12 (-1; +6) month.

## 6 INDIVIDUAL TRIAL PROCEDURES

### 6.1 Screening

All patients that fulfil the inclusion/exclusion criteria and are potential candidates for surgery will be asked to participate in the trial. Those who decline to participate will be documented in the screening failure list along with the reason. To facilitate recruitment, endocrinological/diabetological practices will refer patients to the study centre. The screening failure list will be filled out at these practices.

### 6.2 Patient Information and Informed Consent

Patients will be asked to take part in the study in an outpatient visit. During this visit, potential candidates will be informed about the study and receive information and the consent form. Within a few weeks, patients will be asked to decide whether or not to enrol and questions will be answered prior to agreement to take part in the study. Patients who refuse surgical treatment or where health insurance rejects the application for it but want to participate in the study, can assigned in the observational control group.

The original consent forms will be stored at the trial site; one copy will remain with the patient's clinical sheets and one copy is given to the patient.

The patient's consent refers explicitly to the collection and processing of health-related data. The patient will be informed explicitly about the purpose of collecting the data and scope of what is to be collected and that personal data, in particular those related to health, will be used. All patients are informed about the pseudonymized use or evaluation of the collected data.

#### 6.2.1 Withdrawal of Informed Consent

Patients may withdraw their consent to participate at any time without giving reasons. Nevertheless, the patient should be asked for the reason of the premature termination after being informed that he/she does not need to do so. Information as to when and why a patient was randomized and when he/she withdrew consent must be retained in the documentation.

The patient is to be informed that in case of revocation of his/her consent, the stored data may be used further, as may be necessary to

- guarantee that the patient's personal interests are not adversely affected,
- comply with the requirement to provide complete authorisation documentation.

### 6.3 Enrolment in the Trial (Baseline-Visit) and Randomisation

#### Intervention-Groups:

Immediately after the screening (inclusion/exclusion criteria) and agreement to take part in the study, the patient will be discussed at the interdisciplinary “Board for Bariatric Surgery” and in case of a vote for the study inclusion the responsible medical insurance company will be asked to cover the treatment expenses. After a positive answer of the insurance company to cover the expenses for RYGB the baseline examinations will be performed (see flow chart) and the patient’s data will be given to the trial site.

Patients will be randomised by the trial site and the patients will immediately receive information as to which group they belong to by one of trial staff members.

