### 3 TRIAL DESIGN AND DESCRIPTION

#### 3.1 Trial Design

Open prospective randomized parallel group trial with an additional observational control arm.

The patients in the two surgical arms will not be informed as to which version of the operation they received until completion of the trial whereas, clearly, the control arm cannot be blinded with regard to treatment. If logistically feasible, study visits will be performed by personnel unaware of which surgical procedure was performed.

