#### Observational Control-Group:

All Patients who fulfil the inclusion/exclusion criteria, and

1. admitted to a conservative weight loss programm within the AOP IV-Vertrag in 2016, or
2. received a negative answer of the insurance company to cover the expenses for RYGB or refuse the bariatric surgery and are willing to take part in the study,

will be included in the observational control group (without randomisation).

Examinations will be performed according to the protocol of the interventional groups.

Eligibility of enrolment will be confirmed, and randomisation will be performed at visit 1 (week 0 of the study).

During the enrolment and randomisation visit, the following procedures will be performed

- Obtain medical history, comorbidities, concomitant medication and vital signs and perform physical examination (body weight, BMI, WHR, pulse, RR etc.)
- Routine blood sample (fasting glucose, fasting insulin, fasting c-peptide, HbA1c, serum lipids, Adipokines, inflammatory markers, markers of kidney and liver function etc.)
- Indirect calorimetry (performed either by a nurse or a physician, trained and experienced in this procedure)
- Pregnancy test
- Ultrasound scan (liver, fibroscan, IMT)
- MRI examination by a trained radiologist
- LiMAx test (a functional liver test, will be performed by a medical doctor before and after the preoperative diet)
- BIA-measurement (performed by a trained nurse)
- Diet protocol
- Assess detailed quality of life (SF36) and physical activity (IPAQ)
- Assess Adverse Events since intervention

Whenever blood samples are taken, the scientist or another instructed (laboratory) co-worker will be present to ensure proper further sample management (storage, transport etc.). All samples will be sent to the appropriate lab and stored for further examination.

A detailed description of each procedure is provided in the Working Instructions (WIs).

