#### **Randomisation procedure (RYGB)**

If a patient has signed the Informed Consent form and is eligible for the trial the investigator will proceed as follows:

- Assignment of a Patient-ID: In the patient identification list (PIL, see investigator site file), fill in the patient personal data at the first free position of the list. The Patient-ID printed in the list at this position is assigned to the patient and will be used throughout the study as a pseudonym for the patient.
- Login at the randomisation-site, preferably via the MS Internet Explorer. The user will be asked for the Patient-ID, for check of eligibility criteria, presence of informed consent in writing and stratification items. Enter these items and then click the randomisation button. The system will return to you the intervention arm of the patient.

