1. BMI
  - a.  $\geq 27$  to  $< 50$  kg/m^2
  - b.  $\geq 50$  to  $\leq 60$  kg/m^2
2. Current insulin treatment
  - a. yes
  - b. no
3. Sex
  - a. male
  - b. female

The randomization will be performed centrally by the IFB Data Center and will be computer-assisted, using Pocock's minimization algorithm (1). Before start of recruitment, simulations will be performed to demonstrate that the randomisation procedure given the stratification parameters above yields balanced results. A randomisation ratio of 1:1 will be used.

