## 9.7 Final Analysis

Final analysis will be performed when all patients finished the final study visit, all queries were

answered and the study database was closed.

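### Section 3.1 withholds the type of operation from surgical patients, but Section 6.3 has staff tell them their randomised group at once; both cannot be followed.

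*Protocol*

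**What the plan says.** **Masking (Section 3.1).** The design is described as "Open prospective randomized parallel group trial with an additional observational control arm". The same section then adds masking under that label: patients in the two surgical arms "will not be informed as to which version of the operation they received until completion of the trial". It names the control arm as the one that cannot be blinded. Masking of visit staff is a separate, conditional measure: "If logistically feasible, study visits will be performed by personnel unaware of which surgical procedure was performed".

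**Enrolment (Section 6.3, Intervention-Groups).** After the board vote, the insurer's agreement and the baseline examinations, patients are randomised and "the patients will immediately receive information as to which group they belong to by one of trial staff members".

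**Who learns the arm from the system (Section 6.3, Randomisation procedure).** The investigator enters the patient's data and "The system will return to you the intervention arm of the patient". Nothing is said about passing it on or keeping it back.

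**What is randomised (Sections 6.3 and 9.1).** Patients who refuse surgery, are declined cover by their insurer or come from the 2016 conservative programme "will be included in the observational control group (without randomisation"). For the rest, "A randomisation ratio of 1:1 will be used".

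**The concern.** Section 3.1 states the intention and Section 6.3 is the instruction that staff work from at enrolment. If the two differ, the working instruction is likely to prevail, and a patient who has been told the arm cannot be masked again. A report that relied on 3.1 and called surgical patients blinded would be wrong for anyone handled under 6.3.

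The comparison affected is the randomised one, stRYGB against cllRYGB. Section 9.5.2 gives it enough weight to test it whatever the global result. Knowing the arm could influence:

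- the SF-36, the IPAQ and the diet protocol, which patients complete themselves;
- adverse events, about which patients are asked at each visit (Section 8.1.2);
- the medication part of diabetes remission;
- the decision to go ahead. Surgery may follow randomisation by up to 8 weeks (Section 6.3), and the main analysis is per-protocol (Section 9.5.1). It excludes anyone who did not receive the planned operation or has no primary endpoint value.

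**Working it through.** The point rests on the text, and no power or sample-size formula applies. The check is whether any reading lets both instructions stand.

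**Step 1. What could *group* mean in the 6.3 sentence?**

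| Reading | Evidence in the protocol | Result |
|---|---|---|
| Surgery or control | The sentence follows insurer agreement to pay for the bypass, and it follows randomisation. Controls are not randomised. | Fails: there is nothing of this kind for randomisation to reveal |
| stRYGB or cllRYGB | The randomisation procedure is headed RYGB, the ratio is 1:1, and the heading of Section 5.1 calls each operation a group. | Fits every passage |

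The disclosed group is therefore the version of the operation.

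**Step 2. Set the two instructions side by side.**

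| | Section 3.1 | Section 6.3 |
|---|---|---|
| Who | Patients in the two surgical arms | Randomised patients, who are the same people |
| Information | Version of the operation | Randomised group, which is the same thing (step 1) |
| When told | At completion of the trial | Immediately after randomisation |

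The people and the information are the same and the times differ. No other section reconciles them.

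**Step 3. How many patients?** Section 9.4 plans 68 + 68 = 136 patients in the surgical arms. The synopsis allows up to 20 more under Amendment 5, and Section 15.2 indicates that new patients may be randomised surgical patients or controls. The number concerned is therefore 136, and at most 136 + 20 = 156 if every added patient were randomised.

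**Step 4. Which outcomes are exposed?**

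- *HbA1c at 1 year* is a laboratory value. Knowledge of the arm does not enter the measurement and could act only indirectly, through behaviour or treatment. It is little exposed.
- *Remission* has two wordings. The synopsis and Section 1.1 require that no antidiabetic medication is taken. Sections 2.2 and 9.2.2 require that none is indicated. Patient knowledge can act fairly directly on the first. On the second it acts mainly through what the prescriber learns from the patient.
- *SF-36, IPAQ, diet protocol and adverse event reports* come from the patient and are directly exposed.
- *Withdrawal before surgery* can differ by arm once the arm is known, and the per-protocol analysis drops those patients. The secondary intention-to-treat analysis with multiple imputation limits this but is not the main analysis.

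The protocol gives no figure from which the size of any of these effects could be calculated.

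**The case against.** **The trial is labelled open.** On this view 6.3 is simply consistent with the label. That does not stand: the masking sentence comes under the same label in Section 3.1 and contrasts the surgical arms with the control arm. An open design can mean unmasked surgeons and controls without cancelling an explicit statement about surgical patients.

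**Headings in 6.3 are unreliable.** Some randomisation text does stand under the control-group heading, so the position of the disputed sentence proves little on its own. The reading in step 1 does not depend on the heading alone, because controls are never randomised.

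**The primary endpoint hardly depends on patient masking.** This stands. No hypothesis, test or sample size in Section 9 relies on it, and assessor masking was only ever conditional. A reader might infer that the trial's main result is compromised; the document does not support that.

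**Assessor masking.** A reader might also infer that 6.3 abolishes it. It does not do so directly, although informed patients could reveal their arm at visits.

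**End of masking.** A reader might set Visit 8 at month 120 against a trial duration of 86 months, note that Section 9.7 says "Final analysis will be performed when all patients finished the final study visit", and conclude that the end of masking is wholly undefined. That goes too far. Section 5.2 puts a control patient's completion of the trial at 12 months, Section 1.1 gives a 1-year study follow-up, Section 3.4 gives 1 year per patient, and Section 6.4 describes visits only up to Visit 5. Section 3.4's figures, 74 months of recruitment + 12 = 86, fit the same reading, although the synopsis gives 62 months. What remains open is whether completion in 3.1 means the patient's own month 12 or the end of the whole trial.

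**Conclusion.** The contradiction holds. Sections 3.1 and 6.3 give opposite instructions on the same information for the same patients, and following 6.3 removes the patient masking that 3.1 promises. It concerns the 136 planned randomised patients, and at most 156 with the Amendment 5 additions.

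It should be fixed, but it is not a fault that invalidates the trial. Laboratory HbA1c is little exposed. The patient-reported outcomes, adverse event reporting, the medication component of remission and withdrawal before surgery are more exposed, and the size of any bias in them cannot be derived from the document.

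The conclusion assumes only that *group* in 6.3 means the randomised operation, which is the one reading that fits the other passages. The protocol does not show what patients were actually told. That some or all were unmasked in practice is therefore a possibility to check and not a finding.

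**What to change.** 1. **Section 6.3.** Replace the disclosure sentence with one to this effect: *The allocation returned by the randomisation system is known only to the randomising investigator and the operating team. It is not passed to the surgical patient or, where feasible, to staff who perform study visits, until the completion point defined in Section 3.1.* This fits the existing procedure, in which the system shows the arm to the investigator.
2. **Section 3.1.** State whether completion means the patient's own month-12 visit, as Section 5.2 suggests, or the end of the whole trial.
3. **Patients already enrolled.** If any were told their arm under 6.3, record who and when, report it, and do not describe them as blinded.

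Moving randomisation to the day of surgery might look like a natural addition, but it is not recommended here. It would conflict with randomisation at Visit 1 in the schedule and in Section 6.3. It would also leave open whether BMI and insulin status for stratification are taken before or after the 14-day diet.

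The cost is a wording amendment and a site instruction, plus a check that the patient information says the same. The randomisation system, visits, sample size and analysis stay as they are. Whether the ethics committee must reappraise the change is to be judged under Section 10.3.

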#### Observational Control-Group:

All Patients who fulfil the inclusion/exclusion criteria, and

1. admitted to a conservative weight loss programm within the AOP IV-Vertrag in 2016, or
2. received a negative answer of the insurance company to cover the expenses for RYGB or refuse the bariatric surgery and are willing to take part in the study,

will be included in the observational control group (without randomisation).

Examinations will be performed according to the protocol of the interventional groups.

Eligibility of enrolment will be confirmed, and randomisation will be performed at visit 1 (week 0 of the study).

During the enrolment and randomisation visit, the following procedures will be performed

- Obtain medical history, comorbidities, concomitant medication and vital signs and perform physical examination (body weight, BMI, WHR, pulse, RR etc.)
- Routine blood sample (fasting glucose, fasting insulin, fasting c-peptide, HbA1c, serum lipids, Adipokines, inflammatory markers, markers of kidney and liver function etc.)
- Indirect calorimetry (performed either by a nurse or a physician, trained and experienced in this procedure)
- Pregnancy test
- Ultrasound scan (liver, fibroscan, IMT)
- MRI examination by a trained radiologist
- LiMAx test (a functional liver test, will be performed by a medical doctor before and after the preoperative diet)
- BIA-measurement (performed by a trained nurse)
- Diet protocol
- Assess detailed quality of life (SF36) and physical activity (IPAQ)
- Assess Adverse Events since intervention

Whenever blood samples are taken, the scientist or another instructed (laboratory) co-worker will be present to ensure proper further sample management (storage, transport etc.). All samples will be sent to the appropriate lab and stored for further examination.

A detailed description of each procedure is provided in the Working Instructions (WIs).

